### 3.5 What are the inclusion/exclusion criteria?

For **screening**, inclusion criteria is any healthy term born infant of appropriate weight for gestational age (AGA) based on a Canadian growth reference [1] and born to a generally healthy mother of any race. For the randomized trial, infants must have serum 25(OH)D <50 nmol/L; and for those in the reference group >50 nmol/L. For both the trial and reference groups other **inclusion criteria** are: born to mothers with otherwise healthy pregnancy free of medications that impact vitamin D metabolism (except vitamin/mineral supplements) or fetal growth and intent to breastfeed to at least 3 mo. For the trial we will not exclude on the basis of maternal pre-pregnancy BMI, but will document pregnancy weight gain and obstetrical history from the medical record. For the healthy reference group we will recruit from our screening pool only infants born to mothers of healthy weights (pre-pregnancy BMI 18.5-24.9 kg/m^2) and weight gain according to IOM criteria [2]. **Exclusion criteria** are maternal smoking in pregnancy as it limits growth; and diabetes, preeclampsia, celiac disease, inflammatory bowel disease etc. and medications that impact vitamin D/mineral metabolism. All maternal medications will be documented.

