**Biochemistry Measurements** - Capillary blood samples (0.5 ml) will be collected at screening; but venous sampling (1.0 ml: yields ~500-600 µl serum) used thereafter; samples will be centrifuged (2235 x g for 20 min at 4°C) to obtain serum (for biochemistry) and buffy coat (white blood cells for DNA) and stored frozen at -80°C until analysis. One 5 ml sample will be taken from parents at baseline (fasting) for measurement of serum 25(OH)D and buffy coat saved for future epigenetic work. For infant screening and maternal serum, total 25(OH)D will be measured using a dedicated auto-analyzer in the PI's laboratory (25 µl; 150 µl "dead volume" that is recovered, Liaison Diasorin Inc.); this assay will also be used for safety assessments at 3 and 6 mo, but is not to be used in analyzing the trial data outcomes as it does not capture all of the metabolites. Liquid chromatography tandem mass spectrometry (LC-MS/MS by [name], Queen's Univ.) will be used to measure of 25(OH)D3, 3-epi-25(OH)D3, and 24,25(OH)2D for all time-points from baseline to 36 mo. Briefly, 100 µl of serum will be used for these assays according to our methods [3, 4]. In addition, 1,25(OH)2D (100 µl serum) will be similarly measured using an adapted LC-MS/MS method [5]. Both laboratories are certificated by the Vitamin D External Quality Assessment Scheme and will continue to participate in the National Institute of Standards and Technology quality assurance program. Blood-ionized calcium will be measured immediately using our portable unit (ABL80 FLEX Radiometer Medical A/S, Denmark) and compared to published standards [6]. Remaining sample will be used for IGF-1 (20 µl) using Liaison (Diasorin Inc.); PTH (25 µl; Immotopics Inc CAT#60-3100) and IGFBP3 (20 µl; R&D Systems CAT#SGB300) will be measured by ELISA. Sample for IGFBP3 will be pre-treated with protease inhibitors prior to storage. Plasma total calcium and phosphate (150 µl) and urinary calcium and phosphate:creatinine will be measured in a spot sample collected at each visit during the trial; Beckman Coulter UniCel Dx C600 autoanalyzer as we describe [6]. We will reserve remaining sample for later measurement of C-peptide, propeptide of type 1 collagen (P1NP) as biomarkers related to bone.

**Demographic, dietary and activity survey.** At baseline, parents will be asked to complete a demographic survey regarding their anthropometry, ethnicity and race, income and education

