### 3.16 What is the proposed type of analyses?

Intent-to-treat analyses. All data entry will be audited and baseline characteristics expressed as mean (SD) or median (IQR) depending on normality for continuous data or as proportions for ordinal data (e.g. white non-white, sex). Continuous data for primary outcome measurements will be expressed as mean (95% CI) or proportion (95%CI). All data analysis will be conducted using SAS (version 9.3, SAS Inst. and SAS University Edition). Continuous data for the primary outcome will be examined using mixed model ANOVA accounting for fixed effects (sex,

dosage, time, dosage\*time) and random effects (e.g. infant ID.) with post-hoc testing as applicable (i.e. 2 treatment groups and 1 reference group over 4 time-points) using Tukey-Kramer correction and significant differences accepted at  $p < 0.05$ . The mixed model ANOVA does not require that data be parametric nor of homogeneous variance. Data will be tested using Kolmogorov-Smirnov, Anderson-Darling, or a Shapiro-Wilk tests for normality and where necessary transformed (e.g. log value etc.) to meet the assumptions of the post-hoc tests. The mixed model uses all available data, missing data does not result in omission of an infant's existing data. If more than 5% of data is missing, imputation approaches will be considered. Compliance (unused product and surveyed data) will be compared between groups. For the secondary objectives, a MIXED model will be used for continuous data. The proportion of those achieving the 50 and 75 nmol/L targets will be expressed as a proportion (95% CI) and differences among groups tested using Chi-square analyses or other similar tests based on numbers in each cell or logistic regression. We are experienced in all of these tests [3, 15]. The healthy reference group will be statistically analyzed to form reference curves (e.g., lean mass) using LMS methods [18].

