#### Additional Aspects of Safety Monitoring.

Should an infant be identified with growth failure, defined as crossing major percentiles a report will be sent to the infant's physician for follow-up. Since there are no standards by which to judge infant lean, fat and bone mass, changes in these will be examined. In any withdrawal of treatment scenario, these infants will continue on study unless advised otherwise by the physician and if treatment withdrawal is warranted, they will be followed as intent-to-treat.

461      Table 1. Summary of study measurements and timing

| Measurement                                   | Screening | Baseline | 3
mo | 6
mo | 12
mo | 24 & 36
mo |
|-----------------------------------------------|-----------|----------|---------|---------|----------|---------------|
| Biochemistry                           |           |          |         |         |          |               |
| Total 25(OH)D by Liaison                      | x         |          | x       | x       |          |               |
| Serum vitamin D metabolites by LC-MS/MS       |           | x        | x       | x       | x        | x             |
| 25(OH)D                                       |           |          |         |         |          |               |
| C-3 alpha epimer of 25(OH)D                   |           |          |         |         |          |               |
| 24,25(OH) 2 D                      |           |          |         |         |          |               |
| 1,25(OH) 2 D                       |           |          |         |         |          |               |
| Parathyroid hormone                           |           | x        | x       | x       | x        | x             |
| Ionized calcium, total Ca and PO 4 |           | x        | x       | x       | x        | x             |
| Urinary calcium:creatinine                    |           | x        | x       | x       | x        |               |
| IGF-1 and IGFBP3                              |           | x        | x       | x       | x        | x             |
| Epigenetic mechanisms                         |           | x        | x       |         |          |               |
| Anthropometry                          |           |          |         |         |          |               |
| Weight                                        | x (chart) | x        | x       | x       | x        | x             |

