| July-October 2015  | 
 
Funding notice (July)
 
Steering committee meeting (July)
 
Ethics review (Aug)
 
Students begin program (Sept)
 
Register trial www.clinicaltrials.gov
 
Set up RANDOMIZATION.net
 
Printing of study materials
 
Prepare/receive supplements
 
 | 
All staff are currently available to transfer from other projects.
 
Letter of no objection from Health Canada will be obtained.
 
Euro-Pharm has agreed to provide supplements in kind – see budget page attachments for letter of support.
                                                                                                                                                                                                                                                                                                                                                                                                                                                                                      |
| October 2015-2018  | 
Begin screening recruitment at each hospital's newborn unit (Ethics review in Quebec hospitals is now streamlined so we apply to one site and the others adopt the certificate):
 
 
Ste. Justine Hospital
 
Lakeshore General Hospital
 
McGill University Health Centre (new 2015 Glen site)
 
                      | 
Recruitment is to be overseen by [name]. Study staff and trainees will visit each hospital 5 d a week to recruit for screening. Parent(s) of healthy newborn infants born to generally healthy mothers will be asked if they would like vitamin D status measured as screening for a trial; and if so this would be done using blood taken at the same time as newborn screening. Short demographic and obstetric surveys would be completed. Vitamin D will be measured daily and parents contacted to see if they would like to participate in the trial depending on vitamin D status below 50 nmol/L 25(OH)D or above (reference group). Results of the screening will be given to parents; not thereafter unless safety issues arise.
 |

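### The 50 nmol/L achievement target is also the entry cut-off, and the stated proportion analysis takes no account of the pre-dose LC-MS/MS 25(OH)D

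*Protocol*

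**What the plan says.** - **Entry (Protocol 3.5).** "For the randomized trial, infants must have serum 25(OH)D <50 nmol/L; and for those in the reference group >50 nmol/L".
- **Entry sample and assay (3.9, Biochemistry Measurements).** "Capillary blood samples (0.5 ml) will be collected at screening; but venous sampling" is used thereafter. On the assay: "For infant screening and maternal serum, total 25(OH)D will be measured using a dedicated auto-analyzer in the PI's laboratory" (the Liaison). Table 2 shows that the screening result alone drives the approach to families: "parents contacted to see if they would like to participate in the trial depending on vitamin D status below 50 nmol/L 25(OH)D or above". No confirmatory sample is asked for, and Table 1 schedules no Liaison measurement at baseline.
- **Outcome assay (3.9).** The Liaison serves for safety checks at the 3-month and 6-month visits. The protocol bars it from outcome work: "but is not to be used in analyzing the trial data outcomes as it does not capture all of the metabolites". LC-MS/MS is used "for all time-points from baseline to 36 mo". Table 1 agrees: the row "Serum vitamin D metabolites by LC-MS/MS" is marked from baseline onward. Section 3.4 places allocation at the end of the baseline visit, so this value is pre-dose.
- **Analysis (3.16).** "The proportion of those achieving the 50 and 75 nmol/L targets will be expressed as a proportion (95% CI". Differences among groups are tested by chi-square or similar tests, or by logistic regression. No baseline term or restriction is named for these proportions. Continuous secondary data go into a MIXED model. The same section counts two treatment groups and one reference group.
- **Role (3.8).** Vitamin D status is a secondary outcome.

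**The concern.** The same number, 50 nmol/L, decides who enters and who later counts as having reached the target. Entry uses one sample on one assay; the outcome uses another sample type on another assay. Some infants whose single screening value fell below 50 would have read 50 or more on LC-MS/MS on the day of allocation. As 3.16 is written, they are counted as achievers at later visits.

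Section 2 builds the primary and secondary objectives on correcting low status, so readers will be drawn to take the per-arm proportion at 50 as the share corrected by each dose. Both arms are supplemented, so no within-arm comparison can separate a supplement effect from values drifting back. Randomisation protects the contrast between arms but not the absolute rate in either arm. Infants who were never low on the outcome assay are near-certain successes in both arms and so shrink the difference.

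The reference infants were admitted for reading above 50. If the comparison among groups at 50 includes them, selection decides part of the answer.

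**Working it through.** **Inputs from the protocol.** Entry <50 nmol/L (3.5); targets 50 and 75 nmol/L (3.16); about 24% of infants low (3.12); Liaison may read up to 20% high (Table 3); minimum sample size 66 per group (3.11). The protocol gives no expected value for these proportions, so there is no stated figure to reproduce.

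**Inputs assumed, because the protocol gives none.** Log-normal true 25(OH)D with between-infant CV 35%; independent error CV of 8%, 10% or 15% per sample; Liaison multiplier b = 1.0, 1.1 or 1.2.

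**Step 1: no true change.** On the log scale let s² = ln(1 + 0.35²) = 0.1156 and, at error CV 10%, e² = ln(1 + 0.10²) = 0.00995.
- Total SD = √(0.1156 + 0.00995) = 0.354.
- Correlation between the two readings: ρ = 0.1156/0.1255 = 0.92.
- Screening cut, with 24% below it: h₀ = Φ⁻¹(0.24) = −0.706.
- The same 50 nmol/L on LC-MS/MS: h = h₀ + ln(b)/0.354, which is −0.706 for b = 1.0 and −0.706 + 0.182/0.354 = −0.19 for b = 1.2.
- P(LC-MS/MS ≥50 | screen <50) = 1 − Φ₂(h₀, h; ρ)/0.24.

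Simulation of this model, share of enrolled infants at or above 50 with nothing changed:

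| Liaison reads | CV 8% | CV 10% | CV 15% |
|---|---|---|---|
| no bias | 17% | 21% | 30% |
| 10% high | 5% | 8% | 17% |
| 20% high | 1% | 3% | 9% |

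Under no change this is also the share already at or above 50 at baseline. Counting only infants with baseline LC-MS/MS <50 lowers 21% to 12% (CV 10%, no bias). The restriction reduces regression to the mean but does not remove it.

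**Step 2: both arms gain.** Both arms are supplemented, so Step 1 is a bound and not a forecast. Set additive gains (SD 40% of the mean, assumed) so that 80% and 93% of all enrolled reach 50. Crude proportion minus the proportion among infants with baseline LC-MS/MS <50, in points:

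| Liaison reads | CV 10%: 80% arm, 93% arm | CV 15%: 80% arm, 93% arm |
|---|---|---|
| no bias | 4.4, 1.5 | 6.0, 2.2 |
| 10% high | 1.5, 0.5 | 3.1, 1.1 |
| 20% high | 0.5, 0.2 | 1.5, 0.5 |

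The crude arm difference is 93 − 80 = 13 points. With no bias, among infants low at baseline it is 13 + (4.4 − 1.5) = 15.9 at CV 10% and 13 + (6.0 − 2.2) = 16.8 at CV 15%. That is the dilution.

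**Step 3: sensitivity to the gain.** A second model (total log-SD 0.40, log-scale error SD 0.15, no bias) shows the dependence. Gains of 10 and 20 nmol/L give 60% and 86% in all enrolled, against 50% and 82% in those low at baseline. Gains of 30 and 50 give 97% and 100%, against 96% and 100%.

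**Step 4: type I error.** With 66 per arm and equal no-change proportions of 28%, 18% or 9%, a two-sided 5% test rejects in 4.8-5.1% of runs.

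**Step 5: 75 nmol/L.** With no true change, at most 1.3% of enrolled infants read 75 or more at error up to 15% (total log-SD 0.30-0.50).

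**Step 6: reference group at 50.** In the second model with error 0.10 and no change in anyone, 18.4% of trial infants and 100 − 5.8 = 94.2% of those screened above 50 read at or above 50 on LC-MS/MS. With the Liaison 20% high the figures are 2.5% and 100 − 22.0 = 78.0%. The gap is about 75 points either way, before any dose acts.

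**The case against.** The case on the other side has weight.

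- **Magnitude.** No-change figures do not describe a trial in which every infant is supplemented. Under the 80% and 93% scenario, only one of the twelve values in Step 2 exceeds 5 points. This stands, and it sets the size of the point.
- **Missing inputs.** No CV or population spread is in the protocol. Its one assay-error figure, the Liaison over-reading by up to 20%, makes the problem smaller, because infants below 50 on an over-reading assay are lower still on LC-MS/MS. This stands.
- **Baseline use.** A reader might infer that the pre-dose LC-MS/MS value is wasted. The protocol does not support that: the value is collected for outcome use and continuous vitamin D data go into a MIXED model. Only the proportion analysis gives it no role.
- **Wording.** 3.16 reports a status measure and does not call it a correction rate. That is right, so the harm lies in how the figure will be read.
- **Level of detail.** Covariates for a secondary binary outcome are often left to an SAP, and logistic regression, which 3.16 allows, could carry one. True, but 3.16 already fixes the thresholds, the summary and the choice of tests, and the coincidence with the entry cut-off is visible on the page.
- **Inference.** The randomised contrast is valid and the dilution is conservative. Assumed examples put the power gain from adjustment at only 0.62 to 0.64, or 0.63 to 0.68. The case for adjustment is mainly interpretability.

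None of this answers the selection of the reference group in a test at 50, which needs no assumed CV.

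**Conclusion.** The point holds as a minor one. As 3.16 is written, infants at or above 50 nmol/L on the outcome assay before dosing can be counted as achieving 50, so a per-arm proportion read as a correction rate can be too high and the arm difference somewhat too small. The no-change bound runs from about 1% (Liaison 20% high, CV 8%) to 30% (no bias, CV 15%). With assumed gains giving 80% and 93% at target, the overstatement is about 0-6 points. All of this rests on assumed CVs, spread and gains.

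A reader might go further and conclude that the rate is certainly inflated, or that the dose comparison is biased. The documents support neither. The inflation nearly vanishes if true gains are large or the Liaison over-reads, and type I error between the randomised arms stays near 5%. The 75 nmol/L target and the primary outcome, lean mass, are essentially untouched. The most exposed analysis is a three-group test at 50 nmol/L.

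**What to change.** Amend the wording of 3.16:

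1. Compare the two randomised arms on the 50 and 75 nmol/L targets by logistic regression with baseline LC-MS/MS 25(OH)D as a covariate, keeping all randomised infants.
2. At 50 nmol/L, show the reference group descriptively and leave it out of the test.
3. Print the baseline LC-MS/MS proportion at or above 50 by arm beside each later proportion.

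Optionally, report the 50 nmol/L proportion among infants with baseline LC-MS/MS <50 as a supplementary figure, with a note that this lessens regression to the mean without removing it.

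I would not redefine success as two consecutive visits at or above 50 among infants low at baseline. That drops randomised infants from an intent-to-treat analysis, needs two non-missing samples, and sits badly with an objective about rapid correction by 3 mo.

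Cost: text only. Every sample is already scheduled, and no visits or infants are added.

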### 3.17 What is the proposed frequency of analyses?

For the primary outcome, one analysis will be conducted on blinded groups after all infants have completed 12 mo of study and a second analysis again at 3 y. We wish to keep all of the staff blinded across the entire study. This can be accomplished by generating a database of participants and by removing dates of birth and dates of visit.

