### 3.4 What are the proposed methods for protecting against sources of bias?

Both study products will be blinded to participating families and all researchers. Euro-Pharm will provide these supplements *in kind* in identical containers and the supplement will be identical in color, taste, texture etc. Each bottle will have a unique code to enable tracing back to the product dosage in the rare situation of an adverse event without unblinding the study. Euro-Pharm will provide the blinding codes in sealed envelopes, a copy each for the PI and the medical team. The allocation will be at the end of the baseline visit and care-givers will be educated by a nurse on how to properly give the supplement.

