## 4. Trial management

### 4.1 What are the arrangements for day to day management of the trial?

Refer to Table 2.

**Randomization:** Randomization will be set using RANDOMIZE.net which is a fee-for-service website. It enables randomization according to random block sizes, stratification, 2 treatment arms and verification of entry criteria; and will be used to track non-randomized infants (reference group).

**Data handling:** Two PhD trainees will be responsible for data entry including all screening data and data from visits. Data will be entered after each visit or as soon as when biochemistry data is available; our study co-ordinator (and registered nurse) will audit all of the data and communicate any abnormal findings to the study physicians ASAP. Any abnormal test will be repeated within 24 h and if still abnormal the child will move to standard of care (open label 400 IU/d) and be followed as intent-to-treat.

387 4.2 Describe the trial steering committee and if relevant the data safety and monitoring  
388 committee.

389 Since this trial uses vitamin D within amounts suitable for the general public we will not have a  
390 monitoring committee as required in the past [3]; see section 4.1 data handling above and  
391 **Diagram 2 and Table 3**. Each of the applicants will be a member of the steering committee and  
392 will meet prior to launching the study to review all procedures; then 6-monthly. The safety  
393 committee is comprised of a research nurse, the PI and 3 MDs who are co-applicants. We did not  
394 seek an arm's length safety officer since our dosages are  $\leq$  to the IOM UL. [name] can also  
395 advise if maternal vitamin D status is low.  
396

397 4.3 Describe any risks to the safety of participants involved in the trial.

398 The vitamin D dosages planned in this study are within the UL recommendations set for the  
399 general public by the IOM [19, 20] . We thus believe the risks associated with the interventions  
400 to be minimal. Nonetheless, we will monitor for status until 6 mo of age; the UL for vitamin D  
401 thereafter is higher at 1500 IU/d. The risks associated with blood sampling are minimized by  
402 small volumes. Lastly, dual-energy x-ray absorptiometry (DXA) scans are deemed minimal risk  
403 according to the International Society for Clinical Densitometry [21].  
404  
405  
406  
407  
408  
409  
410

411     Diagram 1: Randomization scheme

[figure not shown]

412  
413  
414  
415  
416  
417  

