| October 2019-      | Complete biochemistry. Complete and clean database on trial.                                                                                                                                                                                                                                                                                                                                  | Begin analysis of data and communicate results. Publish in peer-review journals (open-access format).                                                                                                                                                                                                                                                                                                                                                                                                                                                                                                                                                                                                                                              |
| October 2017-2021  | Complete 2-3 y data points including sampling, biochemical analyses, surveyed information etc. Build and clean database, reporting.                                                                                                                                                                                                                                                           | Communicate results, scientific meetings and peer-review journals.                                                                                                                                                                                                                                                                                                                                                                                                                                                                                                                                                                                                                                                                                 |

Table 3. Normative values and threshold values used in safety monitoring

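### Stripping dates from the database does not by itself keep staff blinded to 3 y once 12-mo results are reported by dose

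*Protocol*

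**What the plan says.** - **Aim.** Section 3.17 on frequency of analyses: "We wish to keep all of the staff blinded across the entire study". Section 3.4 has the same intent: "Both study products will be blinded to participating families and all researchers".
- **First analysis.** Section 3.17: "one analysis will be conducted on blinded groups after all infants have completed 12 mo of study". A second analysis follows at 3 y.
- **Means.** The sentence after the aim reads: "This can be accomplished by generating a database of participants and by removing dates of birth and dates of visit". No other means is given.
- **Calendar.** In Table 2, the row that starts in October 2019 has the trial database completed and cleaned, with the comment "Begin analysis of data and communicate results. Publish in peer-review journals (open-access format)". A separate row, October 2017 to 2021, reads "Complete 2-3 y data points including sampling, biochemical analyses, surveyed information etc".
- **Code custody.** Section 3.4: "Euro-Pharm will provide the blinding codes in sealed envelopes, a copy each for the PI and the medical team". The safety body in section 4.2 ("committee is comprised of a research nurse, the PI and 3 MDs who are co-applicants") includes the PI.
- **Why 3 y counts.** The primary objective in section 2 extends the lean-mass comparison from 3 mo to 3 y.

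**The concern.** The 12-mo analysis can be run on groups labelled A and B, but a paper on 400 versus 1000 IU/d cannot be written until someone says which label is which. From then on, any file that ties a real infant ID to a group label is an allocation list. Birth and visit dates help to identify a child but say nothing about the arm, so removing them does not deal with this risk. Staff who work with study IDs need no dates to recognise an infant.

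The labels may also reveal themselves. Section 3.16 compares the proportions reaching 50 and 75 nmol/L between groups, and that comparison is likely to show which code is the higher dose.

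At stake is the blind for the 2- and 3-year visits. Knowledge of the arm could affect retention effort, decisions to accept or repeat a scan with movement artefact, and the collection of parent-reported diet and activity.

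**Working it through.** **Inputs**
- 148 trial infants over 3 years, given as 4 to 5 per month (section 3.12).
- Recruitment October 2015 to October 2018 (Table 2).
- Visits at 1 wk, 3, 6 and 12 mo, then 2 and 3 y (section 3.7).
- Analysis and publication from October 2019 (Table 2).

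**Reproducing the plan's figures.** 148 / 36 = 4.11 infants per month, within the stated 4 to 5. An infant enrolled in October 2018 reaches 12 mo in October 2019, which agrees with the Table 2 row. Sections 3.6 and 3.7 use the word trial for the period to 12 mo, and Table 2 lists the 2-3 y data separately. That is why the October 2019 row is read as the 12-mo results, although it does not say so.

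**Visits outstanding.** Assume even accrual over months 0 to 36 from 1 October 2015. At month T:
- share of 3-y visits done = (T − 36) / 36
- share of 2-y visits done = (T − 24) / 36, at most 1

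| Date | T | 3-y visits outstanding | 2-y visits outstanding |
|---|---|---|---|
| 1 October 2019 | 48 | 24/36 = 67% (98.7 of 148) | 12/36 = 33% (49.3) |
| January 2020 | 51 | 21/36 = 58% (86.3) | 9/36 = 25% (37) |
| April 2020 | 54 | 18/36 = 50% (74) | 6/36 = 17% (24.7) |
| October 2020 | 60 | 12/36 = 33% (49.3) | 0 |

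**Sensitivity of the 1 October 2019 figure to accrual**
- 4 per month: 148 − 48 = 100 outstanding, 100/148 = 68%.
- 5 per month: 148 − 60 = 88 outstanding, 88/148 = 59%.
- Assumed linear 6-month ramp-up, then constant: accrual is proportional to 3 + 30 = 33 in all and 3 + 6 = 9 by month 12, so 24/33 = 73% outstanding.

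Dropout lowers the counts. It leaves the shares unchanged if it is unrelated to enrolment date.

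**Does the stated means cover the risk?** The model in section 3.16 needs the dosage group and an infant identifier. Section 3.17 removes two date fields and leaves both of these in place. The protocol does not replace study IDs with dummy IDs, say who links codes to doses for the 12-mo report, or keep that link from those who do the later visits.

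**The case against.** **Publication by dose unblinds no infant.** This stands. Group means do not show who received what. The exposure lies in an individual-level file that carries real IDs and group codes.

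**The protocol does plan protection.** It has blinded groups and a stripped database, and the random effect for infant needs only a distinct label, which a dummy ID supplies. This stands in part: the intention is right, but dummy IDs are not stated and what is stated does not hide the arm.

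**Overlap between analysts and visit staff is inferred.** This stands. Section 4.1 has two trainees entering data and a co-ordinator auditing it, and Table 2 places the trial at one research unit. Nothing says that these people receive group codes, run the analysis or perform the 24- and 36-mo scans. A reader might infer that blinding to 3 y cannot hold, or that most 3-y data will be collected by unblinded staff. The protocol supports neither.

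**Two-thirds is an upper-end figure.** Largely stands. The October 2019 row is open-ended, and assays, cleaning and the blinded analysis come before decoding. If these take six months, about half of the 3-y visits remain.

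**The PI's envelope.** A reader might infer that the PI is unblinded. The copies are sealed, and holding a sealed code is not opening it, so there is no breach.

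**This belongs in the statistical analysis plan.** Custody of the link often does. Here, however, the protocol itself names a method for keeping the blind, and that method does not address allocation.

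**Conclusion.** The protocol aims for blinding of all staff to the end of follow-up and fixes a means that does not secure it after the 12-mo groups are decoded. The period at risk covers about two-thirds of the 3-y visits if decoding were immediate in October 2019 (59% to 73% across the accrual assumptions), about half by April 2020 and one-third by October 2020. These shares rest on recruitment running to the Table 2 calendar and on reading the October 2019 row as the 12-mo results.

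They describe how much data is exposed to the risk, not how much will be biased. The likely bias is modest: lean mass by DXA is fairly objective, and supplementation ends at 12 mo, so later knowledge of the arm cannot alter dosing. All 3-, 6- and 12-mo data are collected before the first analysis and are unaffected. The sample size, which rests on 3-mo lean mass, is unaffected too. This is a cheap improvement that protects the 3-y part of the primary objective. It does not undermine the main result.

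**What to change.** In section 3.17, replace the reliance on removing dates with the following:

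1. Run the 12-mo analysis on a file re-keyed with dummy IDs.
2. Have an existing team member who does no visits, scans or data entry keep the ID-to-arm link until the 36-mo data are locked.
3. Release 12-mo results by dose in aggregate only. Exact measurements could still be matched to the source database, so keep the individual-level file from those who do the 24- and 36-mo visits.

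Secondary, in section 3.4: leaving the sealed codes with the medical team alone would fit the statement that all researchers are blinded better than a second copy with the PI. No safety threshold or trigger for unblinding changes.

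The cost is protocol wording and one re-keyed dataset. It should need no extra staff, assuming someone on the team has no visit or data-entry role, and the 12-mo paper is not delayed. The downside is that individual-level data cannot be explored by arm until the 36-mo lock.
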